### Independent Variable

The independent variable in this study is the type of intervention used. This variable has two levels (ie, control and intervention); the *Interventions* section provides more details.

### Confounding Variables

Age, gender, mental health condition, and groups in which the patients are involved during the intervention will be applied, and whether the patients are taking any medication will be analyzed as confounding variables.

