#### Control Group

This group will receive standard care consisting of (1) standard psychiatric nursing care (including some individual counseling), (2) medication trials or titration (antidepressants, antianxiety medicines, sleep medicines), and (3) group therapies (psychoeducation, cognitive behavioral therapy, stress management groups, dialectical behavior therapy, exercise groups, community engagement and wellness groups, leisure groups, and grief and loss groups). Every group runs twice a week for 6 weeks (1.5 months). The patients simultaneously attend 3 therapy groups for 6 weeks. That is, the patients attend 3 therapy sessions per day, twice a week. Each patient attends every group at some point during their 20-week stay in the program. Each group session is 1 hour long. Therefore, the patients receive 36 hours of standard care every 6 weeks for a total of 108 hours on the Short-Term Assessment, Rehabilitation, and Treatment program.

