#### Experimental (Intervention) Group

In the experimental arm, the psychoeducation (Leisure Choices) group therapy (on the Short-Term Assessment, Rehabilitation, and Treatment program) will be replaced by five 3D video screenings (the intervention); in addition, they will receive the same standard care. The five 3D video screening sessions will be delivered as one session per week within a 6-week time frame. Each session will take approximately 1 hour, consisting of one 20-minute video screening and a postvideo screening discussion and questionnaire. A therapist and a member of the research team will be present during the video screening sessions. The therapist will lead the video screening sessions and the postvideo screening discussion (20 minutes of video and 20 minutes of discussion). The research team will observe alertness during video screenings sessions. After the discussion, the research team will administer two questionnaires (Positive and Negative Affect Schedule [PANAS] and postscreening survey), which will take approximately 20 minutes. Each session will take 1 hour overall. The videos will be screened in any order. The goal of these videos is to trigger positive memories, engage individuals, and bring comfort and familiarity. The topics of the videos are as follows: (1) *The Path*, (2) *Remembering*, (3) *The Dance*, (4) *The Memory Box*, and (5) *Baby Animals*. A sample of the videos can be found on the company’s website [15]. The sessions will take place at the Courage Center at Glenrose Rehabilitation Hospital. No more than 5 participants will be present during each video screening session.

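### The therapy groups attended during the intervention are listed as a confounder, yet allocation itself decides attendance at one of them, so any analysis adjusted for that variable would lose or redefine the arm effect

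*Protocol article*

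**What the plan says.** The Confounding Variables section lists age, gender, mental health condition and "groups in which the patients are involved during the intervention will be applied", and ends by saying that "whether the patients are taking any medication will be analyzed as confounding variables". The sentence is grammatically broken, but it places the therapy groups among the confounders and dates them to the intervention period.

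The Experimental (Intervention) Group section states that "the psychoeducation (Leisure Choices) group therapy (on the Short-Term Assessment, Rehabilitation, and Treatment program) will be replaced by five 3D video screenings", with the same standard care otherwise. The Control Group section describes standard care as including "group therapies (psychoeducation, cognitive behavioral therapy, stress management groups, dialectical behavior therapy" and several further groups. On scheduling it says "The patients simultaneously attend 3 therapy groups for 6 weeks" and "Each patient attends every group at some point during their 20-week stay in the program".

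The Independent Variable section names type of intervention, with two levels, as the independent variable. The Data Analyses section invokes intention-to-treat principles, compares arms by the Mann-Whitney U test and changes within arms by the Wilcoxon signed-rank test. It names no adjusted analysis.

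**The concern.** A confounder must not be a consequence of the exposure. The groups attended during the intervention are observed after allocation, and attendance at one of them is set by it: the experimental arm gives up psychoeducation and the control arm keeps it. That attendance is one side of the treatment contrast. Nothing in the article restricts the variable to the groups that allocation leaves alone, or to a schedule fixed beforehand.

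A model with arm and attendance together asks what the videos do at a given attendance at the replaced group. The trial randomises a different question, namely videos in place of that group. The Discussion intends the estimates for sample size calculations in future trials, so an adjusted effect that is inestimable, imprecise or redefined would be carried into that planning.

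**Working it through.** **The plan's own figure.** The Sample Size section gives effect size 1.20, α .05 and power 0.8, hence 12 per group, 24 in total, raised to 30 for 20% dropout. A two-sided t-test needs 11.94, so 12 per group (power 0.802), and 24/0.8 = 30. The figure reproduces, and this point does not change it.

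**Precision cost.** Allocation is 1:1 (Interventions section). Let A be the arm indicator, Z attendance at the replaced group in weeks 12-18, p the share of controls attending, and attendance in the intervention arm zero. Then:
- var(A) = 1/4; P(Z=1) = p/2; var(Z) = (p/2)(1 - p/2)
- cov(A,Z) = 0 - (1/2)(p/2) = -p/4
- r² = (p²/16) / [(1/4)(p/2)(1 - p/2)] = p/(2-p)
- variance inflation of the arm effect = 1/(1 - r²) = (2-p)/(2-2p)

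| p (assumed) | r² | variance inflation | 30 patients are worth |
|---|---|---|---|
| 1/3 | 0.20 | 1.25 | 30/1.25 = 24 |
| 2/3 | 0.50 | 2.0 | 30/2.0 = 15 |
| 1 | 1.00 | infinite | not estimable |

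The article does not state p. The Control Group section implies three six-week blocks (108/36 = 3), so p = 1/3 would apply if each control took the replaced group in one block and the blocks were filled evenly. If every control takes it in weeks 12-18, p = 1 and Z = 1 - A: the design matrix with intercept, arm and attendance has rank 2 of 3.

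**Simulation.** Linear model, 15 per arm, true total effect 1.20 SD, attendance without effect on outcome, 5000 runs per scenario. Adjusted power is among the runs in which the arm effect could be estimated; at most 4% of runs were lost in the scenarios below.

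| attendance, control vs intervention (assumed) | power without adjustment | power with adjustment |
|---|---|---|
| 33% vs 0% | 0.88 | 0.80 |
| 50% vs 0% | 0.89 | 0.72 |
| 80% vs 0% | 0.88 | 0.45 |
| 90% vs 10% | 0.88 | 0.47 |
| 50% vs 50% | 0.889 | 0.875 |

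In all of these the mean adjusted estimate stays near 1.2. The loss is precision: at 90% vs 10% the standard error rises from 0.36 to 0.69.

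**Shift of the estimate.** Now let a share m of the total effect of 1.20 run through loss of the group; m is negative if the group was helping. The adjusted coefficient targets (1 - m) × 1.20. At 90% vs 10% attendance, the expected and simulated values are:
- m = -50%: 1.80 expected, 1.82 simulated
- m = -25%: 1.50 and 1.51
- m = +25%: 0.90 and 0.90
- m = +50%: 0.60 and 0.59

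The unadjusted comparison stays at about 1.20 throughout.

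**The case against.** The strongest reply is that the article contains no model in which this could happen. The stated tests take no covariates, the section does not say how the confounders enter the analysis, and that detail is commonly left to an analysis plan that is not shown. This stands as a limit: the harm is conditional. It does not clear the text, because the section says these variables will be analysed as confounders, and an analysis plan that followed it would inherit the wrong variable.

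A second reply is that the sentence may mean only the other concurrent groups, since arm is named separately and the experimental arm otherwise receives standard care. That reading is possible. The article does not say that allocation changes those groups, and adjusting for them would do little harm if attendance is balanced (0.875 against 0.889 in the balanced scenario). A reader might therefore go too far in inferring that every model following this section must condition on a consequence of allocation. But the wording does not exclude the replaced group.

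Third, p and the displacement shares are assumed. That is so, and they are shown as ranges. At p = 1 the failure would also be visible to the analyst as a term that cannot be fitted.

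**Conclusion.** The point holds in conditional form. The section names as a confounder a variable that in part is decided by allocation, and this is a wrongly stated rule, not an omitted detail. If it is carried out, the arm effect is not estimable when all controls attend the replaced group in weeks 12-18. With partial attendance its variance is inflated by 1.25 at p = 1/3 and by 2.0 at p = 2/3, and the estimate leaves the randomised contrast if loss of the group affects outcome. These sizes assume a linear model with a binary attendance term and attendance shares that the article does not give.

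A reader might infer that the estimate passed to the definitive trial will be wrong in any case. The documents do not support that: the named between-arm test is unadjusted, and if attendance has no effect on outcome, partial overlap costs precision without bias. The point merits correction before analysis but does not undermine the design.

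**What to change.** In the Confounding Variables section, delete the groups attended during the intervention from the list. Limit any adjustment to variables fixed before allocation, such as age, gender, mental health condition and the pre-intervention score already collected, provided that it is taken before the allocation code is released. Medication status can stay if its value is recorded before allocation. Tabulate the groups attended in weeks 12-18 by arm as a description of treatment received. Then reconcile this section with Data Analyses: either name the adjusted analysis that uses these variables or state that they are reported descriptively.

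The cost is a few sentences of wording. The listed characteristics and the pre-intervention score are already planned, and group attendance was to be recorded anyway. What is given up is adjustment for imbalance in the other concurrent groups, which would then be seen only in the table.

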### Participant Timeline

#### Overview

This feasibility trial consisted of a 6-week intervention treatment phase; this study does not have a follow-up phase. The total trial data collection period will be 8 months. As shown in Table 1, Figure 2, and Figure 3, the measurements will be taken as follows.

**Table 1 table1:** Key variables and measurements.

Variables			Participants		Measurement		T_0_		T_1_		T_2_		T_3_		T_5_		T_6_		T_7_		T_8_
**Primary outcome**																					
	GAD-7^a^	Older adults		GAD-7 scale		✓^b,c,d^		✓^c,d^		✓^d^		✓^d^		✓^d^		✓^d^		✓^d^		✓^c,d^	
	HoNOS^e^	Older adults		HoNOS, a clinician rating tool		✓^c,d^		✓^c,d^		✓^d^		✓^d^		✓^d^		✓^d^		✓^d^		✓^c,d^	
	OPQoL-Brief^f^	Older adults		OPQoL-Brief scale		✓^c,d^		✓^c,d^		✓^d^		✓^d^		✓^d^		✓^d^		✓^d^		✓^c,d^	
	PANAS^g^	Older adults		PANAS		✓^c,d^		✓^c,d^		✓^d^		✓^d^		✓^d^		✓^d^		✓^d^		✓^c,d^	
**Secondary outcomes**																					
	Engagement	Older adults		Engagement scale		✓^d^		✓^d^		✓^d^		✓^d^		✓^d^		✓^d^		✓^d^		✓^d^	
	Experiences while watching the 3Scape videos	Older adults and therapists		Semistructured interview																✓	
	MBI-HSS MP^h^	Therapists		MBI-HSS MP																✓	
**Covariates**																					
	Demographics	Older adults and therapists		Self-report assessment questionnaire		✓^c,d^															

^a^GAD-7: Generalized Anxiety Disorder-7.

^b^Outcome present.

^c^Control groups.

^d^Intervention groups.

^e^HoNOS: Health of the Nation Outcome Scale.

^f^OPQoL-Brief: Older People’s Quality of Life-Brief.

^g^PANAS: Positive and Negative Affect Schedule.

^h^MBI-HSS MP: Maslach Burnout Inventory-Human Services Survey for Medical Personnel.

**Figure 2 figure2:**
[figure not shown]
Flow of participants. GAD-7: Generalized Anxiety Disorder-7 item; HoNOS: Health of the Nation Outcome Scale; MoCA: Montreal Cognitive Assessment; OPQoL-Brief: Older People’s Quality of Life-Brief; PTSD: posttraumatic stress disorder.

**Figure 3 figure3:**
[figure not shown]
Study design schema.

#### Intervention Group (Participants: Older Adults)

Research questions 1-2 (primary outcome variables): at the enrollment of the program (week 0 [T_0_], called the pretest program enrollment), the pretest before starting showing the videos (week 12 [T_1_]), and at the posttest when the participants finish the program and watch the videos (week 18 [T_8_]).

Research questions 1-2 (secondary outcome variables): after watching each video, that is, weeks 13-17 (T_1-7_).Research question 3 (participants, older adults): after watching every video (week 18 [T_8_]).

#### Control Group (Participants: Older Adults)

Research question 1-2 (Primary outcome variables): at the enrollment of the program (week 0 [T_0_], called the pretest program enrollment), week 12 (T_1_), and at the posttest when the participants finish the program and watch the videos (week 18 [T_8_]).

For the therapists involved in the intervention group, the measurements will be taken as follows: research questions 4 and 5 (participants, therapists): week 12 [T_1_].

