#### Research Question 4 (Participants: Therapists)

Participants will be asked to participate in a poststudy interview to provide feedback on their experiences, with their patients using the 3Scape videos*.*

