#### Research Question 3 (Participants: Older Adults)

The overall experience, beliefs, and attitudes of older adults while watching the 3Scape videos will be measured using an instrument (8 items on a 5-point Likert scale and 4 open-ended questions) developed by the University of Calgary in a previous study on this technology.

#### Research Question 4

Interviews will be conducted for the therapists. Semistructured questions (topic guided) will examine the usefulness of 3Scape videos for the treatment of the mental health condition of older adults. Interviews will be audiotaped for later analysis by team members. To ensure anonymity, the older adults’ and therapists’ responses will not be connected to their identities. RA 2 will conduct the surveys. The administration of these measures will take approximately 15 minutes.

#### Research Question 5

The MBI-HSS MP will be administered to every therapist who provides the intervention to study the participants at the pretest and posttest. The administration of these measures will take approximately 20-30 minutes. RA 2 will administer these measures.

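### The timeline puts both therapist measurements at week 12, before that cycle's videos, against three other sections and Table 1; the date of the older adults' experience survey also needs clarifying

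*Protocol article*

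**What the plan says.** **Therapists.** The Control Group part of the Participant Timeline ends with the only schedule that the timeline text gives for therapists: "research questions 4 and 5 (participants, therapists): week 12 [T_1". The Intervention Group part defines that week as "the pretest before starting showing the videos (week 12 [T_1", and dates the post-video engagement measurements "after watching each video, that is, weeks 13-17 (T_1-7".

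Other sections say something else:
- Outcome Variables, Research Question 4: "Participants will be asked to participate in a poststudy interview to provide feedback on their experiences".
- Table 1, row "Experiences while watching the 3Scape videos" (older adults and therapists): one tick, at T8 by column count. The MBI-HSS MP row has the same single tick.
- Sample Size, Research Questions 4-5: the therapists to be recruited are those who have delivered the intervention.
- Data Collection Methods, Research Question 5: "The MBI-HSS MP will be administered to every therapist who provides the intervention to study the participants at the pretest and posttest".

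**Older adults.** The Intervention Group part of the timeline states "Research question 3 (participants, older adults): after watching every video (week 18 [T_8", and Table 1 shows experience at T8 only. The Experimental (Intervention) Group section says that after each session's discussion "the research team will administer two questionnaires": the PANAS and a postscreening survey.

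**The concern.** Research question 4 asks about therapists' experiences, beliefs and attitudes regarding the videos. An interview held before the videos cannot supply that. Research question 5 asks whether the videos change caregiver burden, and Data Analyses plans a within-group Wilcoxon signed-rank test on the MBI-HSS MP. That test needs a value before and a value after for each therapist, and one measurement at week 12 gives only the first.

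The sentence at fault is the one that staff would use to book the therapist assessments, so it matters that it is the one that cannot work. The conclusions also list therapists' and older adults' perceptions among the information the study will provide for future adoption.

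For older adults, the article leaves open whether research question 3 rests on one form at the end or on a form from every session. These are different data sets with different denominators.

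**Working it through.** The plan gives no computed figure on this point. The check is a comparison of stated times plus simple counts.

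**Step 1. Where week 12 falls.** Inputs: week 12 is the pretest, and the videos run in weeks 13-17 (Participant Timeline). The intervals from week 12 to the sessions are 13 − 12 = 1, 14 − 12 = 2, 15 − 12 = 3, 16 − 12 = 4 and 17 − 12 = 5 weeks. At week 12, 0 of that cycle's 5 videos have been shown. The timeline labels weeks 13-17 as T1-7 although T1 is week 12 elsewhere, so the check relies on week numbers and not on T labels.

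**Step 2. Research question 4, therapist interview.**

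| Source | Time | After the cycle's videos? |
|---|---|---|
| Participant Timeline, Control Group | week 12 (T1) | no |
| Outcome Variables, Research Question 4 | poststudy | yes |
| Table 1 | T8 (eighth of eight time columns) | yes |
| Sample Size, Research Questions 4-5 | therapists who have delivered the intervention | implied |

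**Step 3. Research question 5, MBI-HSS MP.** With 5-10 therapists planned, the number of pre-post pairs available to the signed-rank test is:

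| Source | Time | Pairs |
|---|---|---|
| Participant Timeline, Control Group | T1 only | 0 |
| Table 1 | T8 only | 0 |
| Data Collection Methods, Research Question 5 | pretest and posttest | 5-10, if all complete both |

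Only the third row supports the planned analysis. Table 1 therefore needs correcting as well as the timeline: it is right for the interview but incomplete for the inventory.

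**Step 4. Research question 3, older adults' survey.** One form at week 18 would come 18 − 13 = 5, 18 − 14 = 4, 18 − 15 = 3, 18 − 16 = 2 and 18 − 17 = 1 weeks after the five sessions. A form in each session is completed on the day. For 15 intervention participants the two schedules yield at most 15 × 1 = 15 or 15 × 5 = 75 forms. The timeline's reference to every video fits the second schedule, and its week-18 date fits the first. No section says that the postscreening survey is the research question 3 instrument (8 Likert items and 4 open-ended questions), so whether the sections conflict or describe two instruments cannot be settled from the text.

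**Step 5. Withdrawal.** Withdrawal From the Study states that a withdrawn participant's information is left out of the analysis. Forms completed in early sessions by someone who later withdraws would therefore be lost, whichever schedule applies.

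**The case against.** The strongest reply is that this is a slip in one line. Every other relevant section places the interview after exposure, and Data Collection Methods gives the inventory both times, so a sensible team would follow those. That is probably true, and it is why the point is a contradiction to reconcile and not a settled plan to interview before exposure.

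A reader might also infer that every therapist interview would precede any contact with the videos. The documents do not support that. Week 12 is on the participant's clock, sessions hold at most 5 people, and 15 participants need at least 15 / 5 = 3 viewing groups. A therapist could have led an earlier group by a later participant's week 12. What stands is narrower: the interview would precede that cycle's videos.

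On the older adults, the reply is that collection in each session may already be planned, and that if the two surveys are different instruments, one end-of-course survey is a legitimate choice. Both are fair. What stands is that the article does not say which applies.

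**Conclusion.** The point holds as an internal contradiction. The week-12 sentence cannot serve research question 4 for the cycle it refers to, and it leaves research question 5 without a posttest: 0 usable pairs, against 5-10 under Data Collection Methods. The T8 reading of Table 1 rests on column count in the extracted text. The contradiction does not depend on it, because Outcome Variables and Data Collection Methods already disagree with the timeline. The research question 3 dating is a lesser matter of clarification.

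Three stronger readings are not supported:
- **That the older adults are surveyed only at week 18.** The intervention section has a postscreening survey in every session, and the timeline wording is ambiguous.
- **That the schedule would miss bad reactions or poor tolerability.** Research questions 3 and 4 name experiences, beliefs and attitudes. The PANAS is collected after each session, engagement after each video, and alertness is observed during screenings.
- **That acceptability would be overstated by a known amount because early stoppers go unsurveyed.** Stopping the videos does not by itself mean missing a week-18 survey. The 20% dropout allowance is not tied to viewing, and the article gives no response rates from which to size a bias.

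**What to change.** 1. **Participant Timeline, therapist sentence.** Put the research question 4 interview at T8, after the therapist's last video session. Put the MBI-HSS MP at pretest (T1) and posttest (T8).
2. **Table 1.** Keep the therapist interview at T8 and add the T1 tick for the MBI-HSS MP.
3. **Research question 3.** State whether the postscreening survey given in each session is the research question 3 instrument. If it is, correct the week-18 date and the Table 1 row, analyse the per-session surveys, and report each session with the number attending as denominator. If it is not, name the two instruments separately and give each its time point.
4. **Withdrawal From the Study.** Reconcile the exclusion of withdrawn participants' information with the use of session surveys completed before withdrawal. Without this, per-session analysis would still lose those forms.

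The cost is wording in the timeline and Table 1, plus entry of up to 5 forms per intervention participant. The time for the session questionnaires is already inside the planned 1-hour session (20 minutes of video, 20 of discussion, about 20 of questionnaires).
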